## Background

The prevalence of type 2 diabetes mellitus (T2DM) is rapidly increasing, making T2DM currently a major health challenge all over the world. Epidemiological studies showed that the T2DM was associated with a 1.5–2.5-fold increased risk of dementia [1]. Mild cognitive impairment (MCI) frequently occurs in T2DM population at a rate of 17.2 % [2] and consequently leads to dementia [3–5]. Moreover, MCI occurs at as early as the prodromal diabetic stage, making the early diagnosis of MCI an important strategy for decision making in T2DM treatment, especially for the prevention of T2DM related dementia.

MCI is currently diagnosed based on clinical criteria [6], mainly the cognition evaluation, however, with bias derived from the subjective nature of these cognition assessing tools. Other relatively objective neuroimaging biomarkers are proposed to detect T2DM related brain alterations that are supposed to be the underlying mechanisms for MCI or dementia. T2DM related MCI may be partly due to neuroanatomical alterations revealed by structural magnetic resonance imaging (sMRI), including atrophy in prefrontal cortex and the anterior cingulate [7–9]. Findings from diffusion tensor imaging (DTI) studies further indicated decreased fractional anisotropy values in frontal white matter [10], cingulum bundle, uncinate fasciculus [11], and anterior limb of internal capsule [12] in T2DM patients. Resting-state functional magnetic resonance imaging (rs-fMRI) studies demonstrated disrupted functional connectivity within the default mode network and decreased spontaneous brain activity in the occipital lobe and post central gyrus in T2DM patients [11, 13, 14]. A most recent study suggested the impaired macromolecular protein pools in fronto-striato-thalamic circuits in T2DM [15]. However, these findings can only be detected at the late stage of T2DM, thus cannot be used to screen MCI at the prodromal diabetic stage.

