### Sample size calculation and statistics

Power calculations have been estimated with reference to other studies that used similar end points [21, 29], according to the formula for estimating the variances of mean values from multiple groups [29]. A sample size of 40 patients per group will be suitable with a power of 0.8, an alpha significance level of 0.05 (two-side). In our group, longitudinal changes of this effect size have been shown previously in groups larger than 10 subjects. Given a drop-out ratio of included subjects, at 25 %, into account, the total sample size is 53 in each group.

Demographic clinical, laboratory, cognitive, and neuropsychological data will be analyzed using SPSS 22.0 (SPSS, Inc.). One-way analysis of variance or *χ*^2^ test will be used to explore differences of these data among three groups (HC, prodromal diabetes and diabetes). Neuropsychological difference among them will be performed with analysis of covariance (ANCOVA) using demographic factors (gender, age, and years of education) as covariates. *Post-hoc* comparisons will then be performed with all demographic factors (gender, age, and years of education) as covariates. *P* < 0.05 is considered as significant. It is reported ReHo and ALFF values are affected by the structure alterations (e.g., atrophy) [30]. We will take ventricular volume as a covariance to rule out such influence.

For images analysis, one-sample t tests will be performed on the individual corresponding maps for each group using SPM12 to explore the differences within groups. Dunnett-*t* test will be performed for differences among case groups and healthy control group. The statistical threshold of the two test will both be set at *P* <0.005 which corresponded to a corrected *P* <0.005 (multiple comparisons with family-wise error).

Linear regression analysis is performed across the T2DM groups and prediabetes groups to assess relationships between imaging values and cognitive testing scores. When the most sensitive parameters are found, a receiver operating characteristic (ROC) curve will be generated to achieve the sensitivity and specificity of the certain parameter for early detection of the cognitive decline.

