## Discussion

The current study evaluates various characteristics of diabetes, especially the central nervous system image presentations in different stage of diabetes progression, and aims to establish an imaging evaluation system for detecting and evaluate MCI in diabetes. Benefits and limitations of this study are discussed below.

It is reported by most researchers that diabetes result in regional hypoperfusion. However, Henry Rusinek and his colleagues found that no hypoperfusion exists in diabetes group, in contrast to hypoperfusion in insulin resistant but not diabetes group [29]. Since insulin resistant is one of main mechanisms of diabetes, we are still uncertain why the perfusion data differs between the two groups. The current study will follow up individual’s characteristics in various areas, especially the image presentation for not less than 3 years. Natural progression of diabetes is monitored. Reperfusion or compensation result in diabetes will be explored. We may discovery the unrevealed mechanism for the divergent between IR and diabetes group.

Structure changes are common in advanced T2DM. It may also exist at prediabetes stage. The volume changes should be used to be one of the covariant to prevent its effect to signal intensity. In current study, we take cerebral ventricle volume, which may represent the structure changes of the whole brain, as a covariant. DKI reveals the non-Gaussian characteristics of gray and white matter [31]. Imaging reports of this respect in diabetes are limited. We undergo the examination of DKI, instead of DTI to explore the real world of microstructure.

Various imaging researches of diabetes have been reported. Most of them are studies of one or two protocols. In our study, multi-modal sequences will be conducted and analyzed at the same time. It may be revealed which one or combined protocols may express the highest area under curve by drawing ROC curve. Corresponding sensitivity and specificity are calculated, and then we will get the cutoff values to diagnose MCI.

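### A single ventricular volume cannot rule out the effect of regional atrophy on ReHo and ALFF maps, so local tissue loss can remain in the group contrast and be read as a functional difference

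*Protocol article*

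**What the plan says.** In the Protocol article, Sample size calculation and statistics, the authors note a report that ReHo and ALFF depend on structural alterations such as atrophy. They then name their remedy: "We will take ventricular volume as a covariance to rule out such influence". The Discussion gives the reason in more cautious terms: "we take cerebral ventricle volume, which may represent the structure changes of the whole brain, as a covariant".

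Four other places bear on this:

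- **Background:** the structural findings cited for T2DM are regional, "including atrophy in prefrontal cortex and the anterior cingulate". The same paragraph closes by saying of the cited imaging findings as a group that "these findings can only be detected at the late stage of T2DM".
- **Discussion:** "Structure changes are common in advanced T2DM. It may also exist at prediabetes stage".
- **sMRI data analysis:** the named volumes are total intracranial, whole brain and ventricular. All three are global.
- **MRI image analysis, rs-fMRI:** ReHo and ALFF are estimated as images, with results expressed in MNI space.

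No regional or voxel-wise grey matter covariate is named anywhere.

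**The concern.** The outcome and the covariate are on different scales. A ReHo or ALFF value belongs to a location, and the structural influence on it is the tissue at or near that location. Ventricular volume is one number per subject. As a linear covariate it removes only the part of local tissue loss that varies with ventricle size. The model then tests for no group difference at a given ventricle size, whereas the stated aim is to find functional differences that atrophy does not explain.

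What is at stake is interpretation. The Background treats structural and functional alterations as separate targets, and the Abstract lists both under the first primary outcome. If residual tissue loss lowers ReHo or ALFF in a case group, the same lesion may be counted once as atrophy and again as functional change.

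This is a stated analysis choice with a stated property, so it is not a detail left to a separate analysis plan.

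**Working it through.** **The plan's own figures.** The protocol gives no figure for how well the ventricular covariate works. Its sample size figure is consistent: 40 evaluable per group with 25% drop-out gives 40 / 0.75 = 53.3, against the stated 53. The calculation below uses n = 40 per group.

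**Assumed inputs.** The protocol gives none of these, so each is a range, with all variables scaled to within-group SD 1:

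- d = local grey matter deficit in the case group, 0.2 to 0.8 SD
- b = correlation between local grey matter and the ReHo or ALFF signal, 0.3 to 0.7
- r = size of the within-group correlation between local loss and ventricular volume, 0 to 0.9
- ventricular enlargement in the case group = r × d
- no direct effect of group on the signal, so every rejection is false

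**Share of the artefact left.** The unadjusted group difference is −b·d. The ventricular covariate gives back b·r·(r·d), so the adjusted difference is −b·d·(1 − r²). The share remaining is 1 − r²:

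- r = 0.3: 1 − 0.09 = 91%
- r = 0.6: 1 − 0.36 = 64%
- r = 0.9: 1 − 0.81 = 19%

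Only r = 1 at every location would justify the claim to rule the influence out.

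**Rejection rate.** In a two-group ANCOVA the residual variance is 1 − (b·r)² and

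SE = √{[1 − (b·r)²] × [2/n + (r·d)² / (2(n − 1))]}, with 2n − 3 = 77 degrees of freedom.

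Worked case, d = 0.5, b = 0.5, r = 0.3:

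- difference = −0.25 × 0.91 = −0.2275
- SE = √{0.9775 × [0.05 + 0.0225/78]} = 0.222
- noncentrality = 0.2275 / 0.222 ≈ 1.03
- rejection from the noncentral t: 17.3% at 0.05 and 3.5% at 0.005

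| d | b | r | at 0.05 | at 0.005 |
|---|---|---|---|---|
| 0.2 | 0.3 | 0.9 | 5.0% | 0.5% |
| 0.2 | 0.3 | 0.3 | 5.7% | 0.6% |
| 0.5 | 0.5 | 0.9 | 5.6% | 0.6% |
| 0.5 | 0.5 | 0.6 | 11.3% | 1.9% |
| 0.5 | 0.5 | 0.3 | 17.3% | 3.5% |
| 0.8 | 0.5 | 0.6 | 21.0% | 4.7% |
| 0.8 | 0.5 | 0.3 | 36.5% | 11.2% |
| 0.8 | 0.7 | 0 | 69.6% | 35.7% |

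A three-group simulation (40 per group, 4,000 replicates) agrees. For d = 0.8, b = 0.5, r = 0.3 it gives 36.0% and 10.9% for T2DM versus controls.

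**With local grey matter as the covariate.** In the same simulation, rejection is 4.7% to 5.4% at 0.05 and 0.3% to 0.7% at 0.005 in every scenario. If grey matter is measured with reliability 0.8 (d = 0.8, b = 0.5, r = 0.3), the rates are 6.6% and 0.8%.

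**At a stricter voxel threshold.** The rates above are for one location at uncorrected thresholds. The plan states a family-wise corrected P < 0.005 for images but gives no voxel cut-off. Assume a cut-off of 0.0001 to 0.00001, with b of 0.4 to 0.6, r of 0.2 to 0.6 and a ventricular shift of 0.3 SD. A single location then rejects in about 0.006% to 0.28% of trials at d = 0.5 and about 0.04% to 2.2% at d = 0.8. These are small in absolute terms but still several times the cut-off. The chance of at least one hit within an atrophic region is higher than at a single location.

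**The case against.** The strongest reply has four parts.

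1. **The size is entirely assumed.** With small deficits and weak signal relations there is essentially no inflation (5.0% to 5.7% at 0.05 in the weakest rows above). This stands. A reader might infer that local tissue loss will produce significant functional findings in this trial. The documents do not support that; they support only that it can.
2. **The cited atrophy is confined to late T2DM.** A reader might infer that prodromal subjects are equally exposed. The Background ties the cited findings to late T2DM, and the Discussion says only that structural change may also exist at the prediabetes stage, without naming a region. This stands and limits the point for the prodromal group.
3. **Images are tested at a corrected threshold.** This also stands, and the 5% to 70% range must not be read as the error rate of the planned image test. Family-wise correction, however, controls chance findings over many voxels. It does not remove a systematic shift in the mean.
4. **Local adjustment may remove real disease effect, and a diagnostic marker judged by ROC need not be free of atrophy.** This has weight as a general argument. But the protocol itself sets out to remove structural influence from ReHo and ALFF, so the covariate should serve that aim. Unadjusted results shown alongside would reveal what adjustment takes away.

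It is also fair to note that the Primary outcome measure section does not name ReHo or ALFF. They fall under it only through the Abstract's broad reference to functional alterations on rs-fMRI.

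**Conclusion.** The point holds as one of residual confounding and overclaiming. One global covariate cannot deliver the property that the statistics section states, and the protocol's own description of ventricle volume as something that may represent whole-brain change does not support it. The bias runs towards reading tissue loss as functional change, most clearly for T2DM versus controls.

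Its size cannot be fixed from the documents. Over the assumed ranges it goes from negligible to serious, and everything depends on the local deficit, the signal relation and the local-to-ventricle correlation. The sample size is not affected. Because the interpretation of rs-fMRI findings is exposed and the repair is an analysis edit, the change should be made.

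**What to change.** In the ReHo and ALFF group models, use grey matter from the 3D-BRAVO segmentation as the structural covariate: the voxel-wise map, smoothed to the same kernel, for image analyses, and the region's own grey matter volume for region means. Report results with and without this covariate, and keep the ventricle-adjusted model as a sensitivity analysis. In the statistics section, replace the claim to rule out the structural influence with one to reduce it.

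The cost is modest extra computing and a revision of the analysis text. The 3D-BRAVO scan and its segmentation are already planned, so no new scans, visits or participants are needed. Each voxel model spends one degree of freedom on the covariate, as it does now. Two small downsides remain. Measurement error in grey matter leaves some confounding (about 6.6% at nominal 5% in the reliability 0.8 case). Adjustment may also remove disease effect that acts through tissue loss, which the unadjusted results would show.

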### MRI image analysis

#### sMRI data analysis

Measurements of total intracranial, whole brain and ventricular volumes will be calculated using volumetric output measures and semi-automated segmentation from FreeSurfer ASEG analysis [23]. Whole brain and ventricular volumes will be normalized to the whole intracranial volume to adjust for variability due to head size. The normalized volumes were used for among group comparisons to evaluate the significant group differences.

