### Primary outcome measure

Network connectivity among multiple brain regions and neuroimaging biomarkers with the 2.5 years’ follow-up at 0.5 year interval. [Time Frame: subjects will be assessed six times (once half a year, up to 2.5 years)]Differences in macro-structural and micro-structural network connectivity among healthy controls, prodromal diabetes and diabetes will be evaluated. These MRI measures include volumetric characteristics (e.g., hyper-intensities, white matter lesions, atrophy), quantitative measures (e.g., T2 relaxation times, mean diffusivity, fractional anisotropy, mean kurtosis), functional characteristics (e.g., activated regions, cerebral blood flow), network properties (e.g., functional and structural connectivity, graph-theoretical measures). [Time Frame: subjects will be assessed six times (once half a year, up to 2.5 years)]

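### The imaging group test names no age, sex or education adjustment, and Dunnett against controls leaves out the prodromal-versus-T2DM contrast that the primary outcome implies

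*Protocol article*

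**What the plan says.** In the protocol article, Sample size calculation and statistics, the cognitive analysis is adjusted: "Neuropsychological difference among them will be performed with analysis of covariance (ANCOVA) using demographic factors (gender, age, and years of education) as covariates". The post-hoc step in the same paragraph is adjusted too: "comparisons will then be performed with all demographic factors (gender, age, and years of education) as covariates".

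A separate paragraph on image analysis gives one-sample t tests within groups, and between groups a Dunnett-t "test will be performed for differences among case groups and healthy control group", both at a family-wise corrected 0.005 level. It mentions no demographic covariate. The imaging adjustments that do appear are ventricular volume for ReHo and ALFF ("We will take ventricular volume as a covariance to rule out such influence") and head-size normalization in sMRI data analysis ("Whole brain and ventricular volumes will be normalized to the whole intracranial volume to adjust for variability due to head size").

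Primary outcome measure defines the target as a three-group comparison: "Differences in macro-structural and micro-structural network connectivity among healthy controls, prodromal diabetes and diabetes will be evaluated". The sections on sMRI data analysis, 3D-pCASL data analysis and Follow up also speak of comparisons among groups or in the three groups. The 3D-pCASL section sets a corrected 0.05 level for CBF.

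The imaging-cognition step is described in one sentence: "Linear regression analysis is performed across the T2DM groups and prediabetes groups to assess relationships between imaging values and cognitive testing scores".

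**The concern.** This is a non-randomized comparison of groups defined by glycaemic status. Subjects inclusion and the abstract restrict age to 40-60 years and require at least senior high school education, but nothing balances the groups within those ranges. If T2DM subjects are older on average than controls, an unadjusted imaging difference mixes diabetes with ageing for any measure that changes with age. The plan accepts this reasoning for cognition but does not carry it to the imaging test, which serves the primary outcome.

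The second issue is coverage. Dunnett's procedure makes two comparisons, prodromal versus control and T2DM versus control. The third pairwise difference, which shows whether alterations progress between the two disease stages, gets no test in the statistics section.

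The pooled imaging-cognition regression matters because the ROC step takes up the most sensitive parameters. If the two groups differ in both mean imaging value and mean score, pooling them without a group term can produce a slope that no within-group relation supports.

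**Working it through.** **The plan's own figure.** 40 evaluable per group with 25% dropout gives 40 / 0.75 = 53.3, against the stated 53. That agrees up to rounding. The 40 cannot be reproduced, because no effect size or SD is given. Solving backwards for two groups of 40, 80% power and two-sided 0.05 gives a standardized difference of about 0.63. That figure is an inference and is used below only as a yardstick.

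**Size of a possible age bias.** None of these inputs is in the article; all are assumptions.
- Correlation r of the imaging measure with age: 0.2 to 0.4.
- Mean age gap between a case group and controls: 3 to 5 years.
- Age SD: 20 / √12 = 5.77 years (uniform over 40-60).

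Bias in SD units = r × gap / age SD:
- low: 0.2 × 3 / 5.77 = 0.10
- high: 0.4 × 5 / 5.77 = 0.35

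**False rejection of a single contrast, no true effect, 40 per group.** Noncentrality = bias × √(40/2): 0.10 × 4.47 = 0.45 and 0.35 × 4.47 = 1.57. With 78 df, from the noncentral t:

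| Nominal level | Critical value | Bias 0.10 | Bias 0.35 |
|---|---|---|---|
| 5% | 1.99 | 7.3% | 34.0% |
| 0.5% | 2.89 | 1.0% | 10.0% |

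The 0.5% row treats the plan's threshold as the level of one test on one regional value. It does not model voxel-wise correction.

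**The same question for the Dunnett pair.** Assumptions: age SD 5.5 years, r 0.3 to 0.5, age rising evenly from controls through prodromal to T2DM. Familywise false-positive rate by simulation:

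| Control-to-T2DM age gap | Nominal 5% | Nominal 0.5% |
|---|---|---|
| 0 years | 5% | 0.5% |
| 2 years | 7-11% | 0.9-1.7% |
| 4 years | 14-31% | 2.3-8.4% |

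The zero row shows that the whole effect depends on an imbalance.

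**Cost of the third contrast.** Three groups of 40, 117 df, power per contrast at an assumed difference of 0.63 (noncentrality 0.63 × √20 = 2.82):

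| Familywise level | Dunnett, 2 contrasts | Tukey, 3 contrasts | Power per contrast |
|---|---|---|---|
| 0.05 | 2.24 | 2.37 | 72% to 67% |
| 0.005 | 3.08 | 3.20 | 40% to 36% |

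**Contrasts and thresholds side by side.** Primary outcome measure: differences among three groups. Statistics section: case groups against controls only, at 0.005. 3D-pCASL data analysis: CBF differences among groups, at 0.05. CBF therefore has two stated levels and possibly two sets of contrasts.

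**The case against.** Several points can be said for the plan.

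- **No imbalance is shown.** A reader might infer that the comparison *is* confounded. The article does not support that. It reports no age gap, and the age range, single recruitment centre and minimum education narrow the scope for one. The risk stands; the fact is not established.
- **The missing contrast may be planned elsewhere.** A reader might infer that prodromal versus T2DM is never examined on imaging. The sMRI, 3D-pCASL and Follow up sections mention among-group or three-group comparisons that could include it. What stands is that the only between-group test named in the statistics section excludes it, and that the sections disagree.
- **The Discussion is not a promise.** It is tempting to cite "We may discovery the unrevealed mechanism for the divergent between IR and diabetes group" as a commitment to this contrast. The sentence voices a hope, and insulin resistance does not define any recruited group. The primary outcome definition is the sound anchor.
- **The text may be looser than it reads.** A ventricular-volume covariate cannot enter a plain Dunnett-t test, so some linear model is implied for ReHo and ALFF, and that sentence follows the demographically adjusted post-hoc step. This makes the text ambiguous for those two measures. It does not help CBF, DKI or connectivity, and neither ventricular volume nor head-size normalization replaces age, sex and education.
- **A condensed article may omit covariates.** This is fair for the regression, where a single sentence excludes nothing. It is weaker for the group test, since the article does specify covariates for one outcome family and names a different test for the other.

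**Conclusion.** The point holds as a weakness of specification in the primary imaging analysis. As written, the imaging group test carries no demographic adjustment in unmatched, non-randomized groups, and it does not deliver all the differences that the primary outcome names. The CBF threshold is stated in two ways.

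The size depends on assumptions. With equal ages the error rates are nominal. With an age-induced bias of 0.10 to 0.35 SD, a single test at nominal 5% rejects about 7 to 34% of the time, and at nominal 0.5% about 1 to 10%. The stricter level lowers the absolute rate but does not remove the inflation, which is about 2- to 20-fold there. The 0.63 yardstick is back-solved and should not be read as the effect that the trial was designed to detect.

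**What to change.** - Replace the Dunnett-t test by a linear model (second-level GLM in SPM12 for maps, ANCOVA for regional values) with group, age, sex and years of education. Keep ventricular volume where it is already planned.
- Test the three pairwise contrasts (control-prodromal, control-T2DM, prodromal-T2DM) with one stated multiplicity adjustment, such as Tukey or Holm.
- Reconcile the contrasts and the significance level across 3D-pCASL data analysis, Sample size calculation and statistics, and Primary outcome measure.
- For consistency, put the same covariates and a group term in the pooled imaging-cognition regression.
- A head-motion covariate for rs-fMRI is optional, since a motion exclusion already exists.

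The covariates are already planned for the cognitive analysis, so no new data are needed. Three covariates cost three degrees of freedom (117 to 114 with 40 per group). The third contrast costs 4 to 5 points of power per contrast, as tabulated above. If that is not acceptable, the plan could keep the two control contrasts as primary, label prodromal versus T2DM as secondary, and reword the primary outcome to match.

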Previous studies suggested that the brain microvascular alterations might explain MCI. A positron emission tomography-computed tomography study revealed that the focal brain blood decrease occured at as early as several years before Alzheimer`s disease diagnosis and was accompanied with the MCI progression [16]. On the contrary, a trend to a slight cerebral blood flow (CBF) increase in bilateral hippocampi and the posterior cingulate gyrus among patients with MCI was noticed using dynamic susceptibility contrast MRI [17]. The major shortcoming of these methods to measure CBF is the use of radio-labeled contrast agents, thus, not suitable for screening brain microvascular alterations in the prodromal diabetic population. Three-dimensional pseudo-continuous arterial spin labeling (3D-pCASL), a non-invasive and non-contrast perfusion imaging method [18], is commonly used to measure CBF alterations and demonstrates equivalent diagnostic performance to Single-photon emission computed tomography (SPECT) for Alzheimer`s disease [19].

Thus, we designed the current prospective diagnostic trial for 2 purposes. First, to investigate the structure, functional alterations and gray/white matter integrity with sMRI, fMRI and diffusional kurtosis imaging (DKI, also measures non-Gaussian diffusion and may provide additional and complementary information to DTI [20]) in prodromal diabetic population, respectively. Second, to investigate the early brain microvascular alterations by using 3D-pCASL.We hope to establish an integrated diagnosing system for early MCI in prodromal diabetic population by using multimodal MRI techniques.

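### The imaging–cognition regression pools T2DM and prodromal participants and names no group term, interaction or prodromal estimate, so it does not by itself support a claim about MCI at the prodromal stage

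*Protocol article*

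**What the plan says.** The section on sample size and statistics gives one sentence to relating imaging to cognition: "Linear regression analysis is performed across the T2DM groups and prediabetes groups to assess relationships between imaging values and cognitive testing scores". Healthy controls are not part of that analysis. The next sentence reads: "When the most sensitive parameters are found, a receiver operating characteristic (ROC) curve will be generated". It gives no criterion for the most sensitive parameter and does not say in which participants the curve is drawn.

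The same section does name adjustment elsewhere. The neuropsychological comparison is an ANCOVA "using demographic factors (gender, age, and years of education) as covariates", and ventricular volume is a covariate for ReHo and ALFF. Nothing comparable is named for the regression.

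On the target population, the Background hopes to "establish an integrated diagnosing system for early MCI in prodromal diabetic population by using multimodal MRI techniques", and the Discussion part of the Abstract also speaks of diagnosing MCI at the prodromal stage. The Background sets earlier T2DM imaging findings aside because "these findings can only be detected at the late stage of T2DM, thus cannot be used to screen MCI at the prodromal diabetic stage". The aim is worded more widely in two places: the Background part of the Abstract speaks of early diabetic MCI, and the main Discussion says the study "aims to establish an imaging evaluation system for detecting and evaluate MCI in diabetes".

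**The concern.** When two groups differ on both a marker and a cognitive score, pooling them creates a correlation even if the two are unrelated inside each group. A slope fitted to T2DM and prodromal participants together can therefore reflect diabetes stage as well as cognition.

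There is a second route that needs no difference in group means. If a marker tracks cognition in T2DM but not in prodromal participants, the T2DM half of the sample can carry the pooled slope to significance.

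Either way, a parameter could go forward to the ROC without any association having been shown in the population named in the Background. The trial could then report a marker and a cut-off for prodromal MCI on evidence that comes wholly or partly from T2DM participants or from the contrast between stages.

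**Working it through.** **Inputs from the protocol article (Sample size calculation and statistics; Background).** 40 evaluable per group, 25% drop-out, 53 enrolled per group, two-sided alpha 0.05, and an MCI rate of 17.2% in T2DM. No MCI rate is given for the prodromal group. No effect size, SD or correlation is given for any marker or score.

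**The plan's own figure.** 40 / (1 − 0.25) = 53.3, so the stated 53 reproduces to rounding. I use both 40 and 53 per group. The 40 cannot be re-derived without an effect size. For scale, 40 per group with 80% power detects a difference between two means of (1.960 + 0.842) × √(2/40) = 0.63 SD.

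**Route 1: stage difference only.** Assume zero correlation inside each group, equal group sizes and within-group SD of 1. Let the groups differ by d1 on the marker and d2 on the score. Pooling adds d1·d2/4 to the covariance and d²/4 to each variance, so

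pooled r = (d1·d2/4) / √[(1 + d1²/4)(1 + d2²/4)].

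For example, at 1.0 and 1.0 SD: 0.25 / 1.25 = 0.20. At 0.8 and 0.5 SD: 0.10 / √(1.16 × 1.0625) = 0.09.

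Share of simulated trials in which the slope is significant at two-sided 0.05 (the true within-group slope is zero, and all separations are assumptions):

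| d1 / d2 (SD) | pooled r | pooled, 40 per group | pooled, 53 per group |
|---|---|---|---|
| 0.5 / 0.3 | 0.04 | about 6% | 6–7% |
| 0.5 / 0.5 | 0.06 | 8% | 9% |
| 0.63 / 0.63 | 0.09 | 12% | 15% |
| 0.8 / 0.5 | 0.09 | 13% | 15% |
| 0.8 / 0.8 | 0.14 | 23% | 29% |
| 1.0 / 0.8 | 0.17 | 32% | 40–41% |
| 1.0 / 1.0 | 0.20 | 44% | 54–55% |

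With a group term in the model, the rate is about 5% in every row.

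**Route 2: association in T2DM only.** Assume no difference in means, correlation 0.4 in T2DM and 0 in prodromal participants. The pooled correlation is then about 0.4 / 2 = 0.20. The pooled slope is significant in 44% of trials at 40 per group and 54% at 53. At a T2DM correlation of 0.5, the figures are about 61% and 74%. A group main effect alone hardly changes this (43% and 53% at 0.4). A test within the prodromal group stays at about 5%. This is why an interaction and a prodromal estimate are needed as well as a group term.

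**What a prodromal-only ROC would rest on.** If the 17.2% T2DM rate also held in the prodromal group, there would be 0.172 × 40 = 6.9, or about 7, MCI cases among 40, and 0.172 × 53 = 9.1, or about 9, among 53.

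**The case against.** The strongest reply is that the article is silent rather than wrong. It does not exclude a group term, and regression covariates are commonly left to a full protocol or SAP. That stands as far as the group term goes: a reader might infer that the plan rules out adjustment, and the text does not say so. The pooled population, however, is stated, and route 2 survives a group main effect.

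Other stronger readings also go beyond the document:

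- *The regression alone picks the marker.* The criterion is not stated, and the Discussion points to AUC: "It may be revealed which one or combined protocols may express the highest area under curve by drawing ROC curve".
- *The regression is the only link between imaging and cognition.* The ROC is itself such a link, and the Discussion also plans to analyse MoCA dimension scores together with imaging.
- *The ROC cut-off will come from a mixed population.* The ROC population is not stated. If it is pooled, the same confounding carries over.
- *T2DM participants are the late-stage disease that the Background calls uninformative.* The Background speaks of late-stage T2DM, not of T2DM as such. This group is aged 40–60, comes from a physical examination centre, and excludes dementia and infarction.
- *The selected marker indexes stage and nothing else.* That is the extreme case. Under modest separations the inflation is small. The Discussion even cites one study that found no hypoperfusion in diabetes but did find it in insulin-resistant non-diabetic people, so large differences between stages cannot be presumed.

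Including T2DM participants also fits the wider aim of detecting MCI in diabetes. That justifies reporting a pooled result, but it does not remove the need for a prodromal estimate when the narrower aim is claimed.

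**Conclusion.** The point holds in a limited form. The plain reading of the text is a pooled regression whose results lead to the ROC, and nowhere does the document name an estimate within the prodromal group, where the Background places the diagnostic aim. A pooled result alone cannot show that a marker detects MCI at that stage.

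The inflation from stage difference ranges from negligible to severe. It is slight near 0.5 and 0.3 SD, and becomes serious from about 0.8 SD on both variables. These figures rest on assumed separations, normal data and no within-group association. The T2DM-only route rests on an assumed correlation of 0.4 or 0.5 in that group. The document supports none of these values over the others, so the figures show what could happen, not what will. This should be put right in the analysis plan; it does not invalidate the design.

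**What to change.** Include glycaemic group and a group-by-marker interaction in the imaging–cognition regression. Report the within-prodromal slope with its confidence interval. State in which participants the ROC is drawn, and report sensitivity and specificity in the prodromal group alongside the pooled result. Claim a prodromal MCI marker only if the prodromal estimate supports it.

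The cost is analysis wording; no new data are needed. The drawback is precision. With the few prodromal MCI cases estimated above, sensitivity and any cut-off would have wide intervals, and choosing among many MRI parameters on those cases alone would be unstable. For that reason selection need not be restricted to the prodromal group, provided that the prodromal result is shown and the claim is limited to what it supports.
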